**Methods:**

Role of ARNi in Ventricular Remodeling in Hypertensive LVH (REVERSE-LVH) is a prospective, randomized, open-label, blinded endpoint (PROBE) clinical trial. Adults with hypertension and left ventricular hypertrophy (LVH) according to Asian sex- and age-specific thresholds on cardiovascular magnetic resonance (CMR) imaging are randomized to treatment with either sacubitril/valsartan (an ARNi) or valsartan (an ARB) in 1:1 ratio for a duration of 52 weeks, at the end of which a repeat CMR is performed to assess differential changes from baseline between the two groups. The primary endpoint is the change in CMR-derived diffuse interstitial fibrosis volume. Secondary endpoints include changes in CMR-derived left ventricular mass, volumes, and functional parameters. Serum samples are collected and stored to assess the effects of ARNi, compared with ARB, on circulating biomarkers of cardiac remodeling. The endpoints will be analyzed with reference to the corresponding baseline parameters to evaluate the therapeutic effect of sacubitril/valsartan vs. valsartan.

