#### Sample size calculation

2.4.1.

We determined that a sample size of 35 participants per group would provide the trial with 80% power at a 5% significance level (two-sided) to detect an absolute minimum difference between treatment groups of 3.5 mL/m^2^ in terms of change in interstitial volume from baseline following 52 weeks, assuming an SD of 5.8 mL/m^2^ [data that was subsequently published (25)] and a moderate correlation of 0.60 between interstitial volumes at baseline and 1 year. The effect size was based on an estimate of the magnitude of myocardial fibrosis regression that could be expected to translate into improved clinical outcomes (5). The study plan is to randomize 80 participants, allowing up to 15% dropout and treatment discontinuation.

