#### Statistical analysis

2.4.2.

The analyses will be based on the intention-to-treat principle, such that all participants will be included in analysis according to their assigned treatment groups.

Baseline characteristics and changes in CMR endpoints between the two treatment groups will be compared. If significant baseline differences are found between the two groups, appropriate modifications to analytical methods may be made to adjust for the differences. Categorical variables will be compared with *χ*^2^ test and described as count (percentage). Continuous variables that are normally distributed will be compared using the parametric Student’s *t*-test and presented as mean ± SD. If the normality assumption is not met, they will be compared using the non-parametric Mann–Whitney *U* test and described as median (interquartile range). All analyses will be performed two-sided at the 5% significance level. A *p*-value of <0.05 will be considered statistically significant. Additional exploratory analyses may be performed.

Statistical analyses will be performed using SPSS (IBM SPSS Inc., NY, USA) and GraphPad Prism (GraphPad Software, Inc., CA, USA).

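### The primary test may switch from means to medians on the trial's own data, while the trial is sized on a 3.5 mL/m² difference in mean change; one baseline-adjusted mean difference should be fixed instead

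*Protocol article*

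**What the plan says.** The abstract defines the outcome: "The primary endpoint is the change in CMR-derived diffuse interstitial fibrosis volume". Section 2.4.2 (Statistical analysis) announces a comparison of the groups on baseline characteristics and on changes in the CMR endpoints. It then gives a single rule for continuous variables. Those that are normally distributed get Student's t-test and mean ± SD. For the rest, "If the normality assumption is not met, they will be compared using the non-parametric" Mann–Whitney U test, with median and interquartile range. No separate method is named for the primary endpoint, so the rule governs it. The same section allows methods to be modified if baseline differences turn out significant.

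Section 2.4.1 (Sample size calculation) states that "a sample size of 35 participants per group would provide the trial with 80% power at a 5% significance level (two-sided"), the target being "an absolute minimum difference between treatment groups of 3.5" mL/m² in change from baseline. It does so "assuming an SD of 5.8 mL/m^2"² and "a moderate correlation of 0.60 between interstitial volumes at baseline and 1 year".

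**The concern.** Which test is primary depends on how the outcome data look once they are in. If the switch fires, the result becomes a rank test with two medians. Section 2.4.1 presents 3.5 mL/m² as a degree of regression expected to matter clinically, so readers will hold the result against that figure. Medians of change are also in mL/m², but the gap between them is a different quantity from the difference in means, and the two agree only under certain shapes. A plain Mann–Whitney test also has no place for the baseline value, although section 2.4.2 foresees that baseline adjustment might be wanted.

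**Working it through.** **Inputs from section 2.4.1:** difference 3.5 mL/m², SD 5.8 mL/m², correlation 0.60, two-sided 5%, 80% power, 35 per group.

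**1. Which quantity was the trial sized on?** Use n per group = 2 × (1.960 + 0.842)² × SD² / 3.5².

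| SD used | Value | n per group |
|---|---|---|
| Change score: 5.8 × √(2 × (1 − 0.60)) | 5.19 | 34.5, so 35 |
| 5.8 directly | 5.80 | 43.1, so 44 |
| Baseline-adjusted: 5.8 × √(1 − 0.60²) | 4.64 | 27.6, so 28 |

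Of these, only the unadjusted comparison of mean change gives the stated 35. Its exact t-test power at 35 per group is 79.5% (normal approximation 80.6%).

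**2. How often would the switch fire by chance?** The article names no normality check, so this is assumed. A 5% Shapiro–Wilk test in each arm fires on normal data with probability 1 − 0.95² = 9.75% (simulated: about 10%). A single 5% test on pooled residuals fires in about 5%. The range is therefore about 5% to 10%; a graphical check could differ.

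**3. Does the switch harm error rate or power?** Simulation: 35 per arm, SD of change 5.19, per-arm Shapiro–Wilk, 10,000 trials per row, same shape in both arms.

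| Shape | Switch fires | Type I error: t-test / with switch | Power at 3.5: t-test / with switch |
|---|---|---|---|
| Normal | about 10% | 5.0% / 5.1% | 79.5% / 79.5% |
| t, 4 df | about 60% | 4.8% / 4.9% | 80.9% / 88.7% |
| Lognormal, sigma 0.8 | about 100% | 4.5% / 4.9% | 81.3% / 99.0% |

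In a further run of 20,000 normal trials, the significance verdict differed from that of an always-used t-test in 0.35% of trials under the null and 0.9% at 3.5 mL/m².

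**4. Can the reported quantity move?** Suppose a fraction of treated patients respond and the rest do not, with the mean difference held at 3.5 mL/m² and a spread of 5.19 around each patient's expected change. With 25% responding, each responder gains 3.5 / 0.25 = 14 mL/m². The treated median m then solves 0.75 Φ(m/5.19) + 0.25 Φ((m + 14)/5.19) = 0.5. At m = −2.16 the left side is 0.75 × 0.339 + 0.25 × 0.989 = 0.501, so m is about −2.2, against a control median of 0.

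| Responding | Mean difference | Median difference | Hodges–Lehmann shift |
|---|---|---|---|
| 25% | 3.5 | about 2.2 | about 2.7 |
| 33% | 3.5 | about 2.9 | about 3.2 |
| 50% | 3.5 | about 3.5 | about 3.5 |

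This is an illustration, not a forecast. In the 25% case the treated arm's variance is 26.9 + 14² × 0.25 × 0.75 = 63.7, an SD of about 8.0, well above the planned 5.19.

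**5. What would a baseline-adjusted mean difference give?** At 35 per group the noncentrality rises from 3.5 / (5.19 × √(2/35)) = 2.82 to 3.5 / (4.64 × √(2/35)) = 3.16. Power rises from 79.5% to about 87.5%.

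**The case against.** The strongest defence is that the rule is stated in advance, the CMR readers are blinded, and the operating characteristics are sound. That stands. A reader might infer that choosing the test from the data inflates type I error or loses power; the simulations do not support this. With heavy tails or strong skew and a pure shift, the switch even gains power, while the t-test keeps about the power planned.

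A reader might also infer that the switch costs the trial the step from 79.5% to 87.5% power. It does not: the default branch is an unadjusted t-test, so that gain is absent whether or not the switch fires.

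Nor is it right that the Mann–Whitney branch yields nothing comparable with 3.5 mL/m², or rules out adjustment altogether. Medians are on the same scale and agree with the mean difference under a pure shift. Section 2.4.2 permits modified methods, and rank-based ANCOVA exists. The t-test branch names no between-group estimate or interval either, which an article may leave to the full protocol or analysis plan.

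What the defence does not answer is that the written rule leaves the primary quantity to be settled by the data. When shapes differ, that quantity is no longer the one the sample size was built on.

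**Conclusion.** The point holds as one of interpretation and pre-specification, of modest weight. The sample size reproduces as a comparison of mean change, yet the analysis rule can replace that comparison with medians. The possible gap is zero under a pure shift and about 1.3 mL/m² (3.5 − 2.2) in the 25% responder example, which rests on an assumed response pattern. The 5% to 10% chance switching rate rests on an assumed check. In those chance switches on normal data with a pure shift, mean and median differences target the same value, so the cost there is small. No finding of distorted error rates follows. The case for change is that fixing one mean-based, baseline-adjusted analysis removes the ambiguity and, separately, improves power under the plan's own inputs.

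**What to change.** Replace the conditional rule, for the primary endpoint, with wording such as: *The primary analysis estimates the difference between groups in mean change in indexed interstitial volume at 52 weeks, in mL/m², by ANCOVA adjusted for the baseline value, with a 95% confidence interval. It is reported whatever the distribution of the data. A Mann–Whitney comparison of change is a sensitivity analysis and does not replace it.* State now whether the interval uses heteroscedasticity-robust standard errors or a bootstrap.

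The cost is analysis wording only. Baseline and 52-week CMR are already scheduled, and no extra participants are needed (28 per group would suffice for 80% power under the plan's inputs). One thing is given up: with strong skew and a pure shift, the rank test would be the more powerful primary test. The sensitivity analysis would still show that result. If an analysis plan already fixes a single method, the rule in the article should be brought into line with it. The change should be made before outcomes are compared by treatment group.

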## Discussion

3.

### Significance

3.1.

To the best of our knowledge, REVERSE-LVH is the first trial that examines the anti-fibrotic potential of sacubitril/valsartan in a clinical population, guided by imaging. Whilst pre-clinical data support that sacubitril/valsartan combination is more effective in regressing hypertrophy and fibrosis compared with ARB such as valsartan (13, 26), our work will verify such benefits in the clinical setting. Importantly, this study will provide possible mechanistic insights into the clinical benefits of sacubitril/valsartan in HF as observed in the pivotal PARADIGM-HF (7) and PARAGON-HF (27) trials.

Myocardial fibrosis, a hallmark of HF, has shown regression on histology with lisinopril and losartan in HHD (4, 5), torasemide in hypertensive HF (28), and spironolactone in non-hypertensive HF (29). Building upon these findings, REVERSE-LVH aims to further enhance our understanding of HHD by focusing on treatments specifically targeting myocardial fibrosis. As this field advances, new therapeutic targets will emerge, and more specific agents will be developed. The role of CMR in monitoring disease progression and evaluating treatment response is expected to evolve, providing valuable insights into the effectiveness of fibrosis-targeted therapies. Our subsequent exploration of circulating fibrosis biomarkers would potentially complement the imaging evidence with regard to mechanism elucidation as well as improvement of treatment monitoring strategy via a multi-marker approach.

Our study population comprises hypertensive individuals with LVH free from overt HF and other cardiovascular conditions. We have demonstrated in the REMODEL study that 28% of adults with hypertension have LVH. The proportion of LVH doubles in the presence of both hypertension and diffuse interstitial fibrosis (24). This, along with the notion that LVH confers increased risk of HF, highlights the substantial hypertensive population that will potentially benefit from the findings of the REVERSE-LVH trial.

### Design

3.2.

This trial is conducted in a PROBE design that is more reflective of real-world clinical practice, less costly whilst delivering the advantages of classic double-blinded studies (30). Although a double-blinded design is maximally robust with respect to bias, it requires the commercial production of blinded medications and also adds difficulty to titration of medications as treating clinicians are blinded from the medication allocation and dosages. A PROBE study design, used in many hypertension trials, involves treatment known to participants and clinicians as in standard care practice, enables scientific investigation with stringent randomization, and eliminates bias with blinded endpoint evaluation.
